# Assertive community treatment for high-utilizing alcohol misuse patients: a before-and-after cohort study protocol

**DOI:** 10.1186/s12913-023-10516-5

**Published:** 2024-02-28

**Keywords:** Alcohol-related frequent attenders, Emergency department utilization, Assertive community treatment, Healthcare resource optimization, Singapore

## Abstract

**Background:**

The challenge posed by Alcohol-Related Frequent Attenders (ARFAs) in Emergency Departments (EDs) is growing in Singapore, marked by limited engagement with conventional addiction treatment pathways. Recognizing this gap, this study aims to explore the potential benefits of Assertive Community Treatment (ACT) - an innovative, community-centered, harm-reduction strategy—in mitigating the frequency of ED visits, curbing Emergency Medical Services (EMS) calls, and uplifting health outcomes across a quartet of Singaporean healthcare institutions.

**Methods:**

Employing a prospective before-and-after cohort design, this investigation targeted ARFAs aged 21 years and above, fluent in English or Mandarin. Eligibility was determined by a history of at least five ED visits in the preceding year, with no fewer than two due to alcohol-related issues. The study contrasted health outcomes of patients integrated into the ACT care model versus their experiences under the exclusive provision of standard emergency care across Hospitals A, B, C and D. Following participants for half a year post-initial assessment, the evaluation metrics encompassed socio-demographic factors, ED, and EMS engagement frequencies, along with validated health assessment tools, namely Christo Inventory for Substance-misuse Services (CISS) scores, University of California, Los Angeles (UCLA) Loneliness scores, and Centre for Epidemiologic Studies Depression Scale Revised (CESD-R-10) scores.

**Discussion:**

Confronted with intricate socio-economic and medical challenges, the ARFA cohort often grapples with heightened vulnerabilities in relation to alcohol misuse. Pioneering the exploration of ACT’s efficacy with ARFAs in a Singaporean context, our research is anchored in a patient-centered approach, designed to comprehensively address these multifaceted clinical profiles. While challenges, like potential high attrition rates and sporadic data collection, are anticipated, the model’s prospective contribution towards enhancing patient well-being and driving healthcare efficiencies in Singapore is substantial. Our findings have the potential to reshape healthcare strategies and policy recommendations.

**Trial Registration:**

ClinicalTrials.gov, NCT 04447079. Initiated on 25 June 2020.

**Supplementary Information:**

The online version contains supplementary material available at 10.1186/s12913-023-10516-5.

## Background

Globally, in 2016, alcohol consumption ranked as the seventh primary cause for both mortality and Disability-Adjusted Life Years (DALYs), attributing to 2.2% of deaths in women and 6.8% in men. Almost one-tenth of worldwide deaths among the age group 15–49 years can be ascribed to alcohol consumption [1].

Patients who frequently utilize emergency department (ED) services due to alcohol-related issues are referred to as alcohol-related frequent attenders (ARFAs) [2]. These patients, often characterized by chronic alcohol misuse, constitute a small fraction of the ED population but disproportionately consume substantial emergency medical resources, including emergency medical services (EMS), EDs, and inpatient services [3, 4].

ARFAs not only present with acute symptoms of alcohol intoxication but also the long-term effects of alcohol misuse such as withdrawal symptoms, gastrointestinal bleeding, and complications of liver cirrhosis. Given the time-sensitive nature of EDs and the competing priorities therein, physicians often struggle to provide sustainable and long-term interventions to curb alcohol misuse in these patients [5].

Despite recommended treatment regimens for addiction, ARFAs frequently default, particularly within the initial three months. Data has suggested that this group of patients have high drop-out rates when referred for treatment [6]. Instead, this patient group often reverts to utilizing the ED and EMS, resulting in unplanned hospital admissions due to alcohol-related complications.

The acute and chronic presentations of ARFAs pose significant challenges, requiring substantial resources for close monitoring to prevent falls, dealing with potential staff abuse, cleaning services, and handling prolonged stays in crowded departments [7, 8]. Moreover, chronic alcohol misuse often leads to high-risk conditions like variceal bleeding and liver failure, thus escalating morbidity and mortality rates [9].

While extensive research on interventions for ARFAs [10], predominantly Case Management (CM), has been conducted in Western countries [11–13], few have explored the impact of assertive community treatment (ACT): a patient-focused, community-based approach which emphasizes the delivery of comprehensive and personalized services to patients.Despite a rigorous evidence base for CM, it has demonstrated variable reductions in ED use by ARFAs [14]. 

There is also a paucity of understanding regarding the characteristics of ARFAs and their response to ACT intervention.

This paper describes the study protocol of an interventional trial designed to investigate the effectiveness of ACT in managing ARFAs. We aim to detail the methods and considerations guiding the investigation, particularly focusing on the utilization of ACT within local contexts. The protocol considers the multifaceted needs of ARFAs, proposing comprehensive, community-based interventions that extend beyond traditional ED care.

Our intention is not only to present a structured and replicable study design but also to contribute to the ongoing discourse surrounding alcohol misuse treatment. By outlining the protocol in this paper, we seek to facilitate a broader understanding of ACT’s potential impact on ARFAs, offering insights that may inform future initiatives, policies, and research endeavours in managing problematic drinking behaviours, thus reducing dependency on EDs.

## Methods

### Study design

This study is conducted as a prospective, multi-centre, before-and-after cohort study, comparing the outcomes of ACT interventions to standard emergency care among ARFAs from four adult EDs across Singapore (see Fig. 1).

**Fig. 1 Fig1:**
[figure not shown]
Study design with inclusion and follow-up timetable

### Objectives

To conduct a before-and-after trial of ARFAs in four public hospitals under three healthcare clusters in Singapore.To evaluate the effectiveness and cost-effectiveness of ACT intervention for ARFAs as compared to standard care in the emergency departments.To describe the patient characteristics, ED care characteristics and health outcomes of ARFAs.

### Primary hypothesis

ACT is expected to be more effective than standard care in reducing the annual number of ED visits by ARFAs, as measured at a 12-month follow-up.

### Secondary hypotheses

ACT is expected to improve health outcomes compared with standard care at a 12-month follow-up.ACT is expected to be more cost-effective compared with standard care at a 12-month follow-up.

The study protocol comprises a total of 17 visits, including a follow-up at six months post-final assessment. The intervention manual and comprehensive study protocol is adhered to the Standard Protocol Items: Recommendations for Interventional Trials (SPIRIT) attached in Additional file 1 (see Additional file 1) and can be made available upon request from the authors.

Employing a before-and-after study design will facilitate measurements of ACT outcomes in ARFAs before and after its formal implementation in EDs. Changes in ARFAs’ outcomes will thereby be attributed to the ACT intervention. Previous ARFAs ED usage data serves as a control group for comparative analysis. While this design does not negate the need for randomization, it offers a more pragmatic approach that can be less resource-demanding than a randomized-controlled trial (RCT). Importantly, the study can be executed concurrently with standard ED operations.

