### Participants

#### Inclusion criteria

Patients at the study site meeting the following criteria are eligible for participation: aged 21 years or older, have recorded a minimum of two alcohol-related and five all-cause visits to an ED in the preceding 12 months, and are fluent in either English or Mandarin. Patients who discontinued ACT but have completed a minimum of three ACT visits are included, considering that significant interventions would have been implemented into their social, drinking, and medical conditions by the third visit.

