#### Screening and recruitment

Patients who meet the inclusion criteria are identified through clinical referrals within each participating hospital using alcoholism codes ICD-10-AM, SNOMED and ICD-9-CM codes. Each hospital’s ACT teams prioritize recruitment for those who have most frequently used ED services, with the aim to recruit up to 17 patients over six months (equating to 34 patients per year).

Four hospitals participate in the study over a four-year period (see Table 1). Recruitment of participants for each site is done yearly and staggered. Considering Singapore’s limited resources, and the existence of only one tertiary addiction centre, the study initiation dates are strategically staggered to ensure sufficient supervisory support.

**Table 1 Tab1:** Details of recruitment

Intervention Site	Date of Initiation	Date of completion	Maximum Subjects
Hospital A	August 2020	February 2024	136
Hospital B	August 2021	February 2024	102
Hospital C	August 2022	February 2024	68
Hospital D	August 2023	February 2024	34

Invitations to partake in the study are extended via phone calls, offering potential subjects a week for consideration. However, pilot data suggest a significant proportion of ARFAs are homeless and lack phone access. As such, an opportunistic recruitment approach is primarily adopted, enabling engagement with eligible patients during their hospital visits. Members of the study team approach eligible patients, extending an invitation to participate and providing necessary information, including the need for retrospective data sharing consent. The consent is obtained by either Site-Principal Investigators (PIs) or Co-Investigators (Co-Is).

To optimize participant retention and ensure complete follow-up, we have implemented strategies that emphasize flexibility and participant engagement. Regular check-ins, either by phone or text, will maintain consistent communication, while appointment schedules are tailored to participants’ availabilities. If participants discontinue or deviate from the intervention protocol, we will attempt an exit interview to gather insights and continue collecting relevant outcome data, ensuring that their contribution remains valuable and meaningful to the study.

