#### Primary outcome: number of ED visits

The primary outcome is the number of ED visits by ARFAs, sourced primarily from the electronic records system of the participating hospitals. A comparative analysis will be conducted between the rates of ED visits pre-intervention (12 months) and post-intervention (12 months).

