### Statistical methods

Continuous variables will be reported as mean and standard deviation using Student’s t-test. Categorical variables will be reported as frequency count and percentage using Chi-square test/Fisher’s exact test. Univariate analysis will be done to select variables for an adjusted multivariable analysis. Statistical significance will be set at P < 0.05 criteria. We will adopt imputation to address missing data.

Using complete set data analysis, cases undergoing ACT will be compared their own historical outcomes as controls. ED utilizations will be compared using the paired sample t-test or Wilcoxon Signed Rank test, the post-intervention utilization of ARFAs undergoing ACT will be compared to the pre-intervention utilization.

To adjust for potential confounders, multivariable regression analysis will be undertaken. Interactions will be tested for variables that are clinically relevant and are statistically significant. Model adequacy will be assessed through coefficients of determination (R2) and by plotting error terms against predicted values. Presence of multicollinearity will be evaluated by variance inflation factor (VIF). Should complete set analysis show efficacy, we will proceed to analyze the data using an intention-to-treat analysis.

The incremental costs of delivering the intervention will be estimated and compared to any observed cost savings from reduce usage of ED services and other health services. All analyses will be performed using R 4.2.0 (www.r-project.org) and STATA version 17.0 (StataCorp. 2017. Stata Statistical Software: Release 17.0. College Station, TX: StataCorp LLC) software.

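### The year that qualifies patients as heavy users is also their baseline, so part of any fall in ED visits will be regression to the mean, yet the protocol attributes the change to ACT

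*Protocol article*

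**What the plan says.** Under Inclusion criteria, patients must "have recorded a minimum of two alcohol-related and five all-cause visits to an ED in the preceding 12 months". Under Screening and recruitment, the ACT teams "prioritize recruitment for those who have most frequently used ED services". The same section says that "an opportunistic recruitment approach is primarily adopted, enabling engagement with eligible patients during their hospital visits".

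The primary outcome section compares the "rates of ED visits pre-intervention (12 months) and post-intervention (12 months"). The design rationale under Secondary hypotheses states that "Previous ARFAs ED usage data serves as a control group for comparative analysis", and Statistical methods repeats that "cases undergoing ACT will be compared their own historical outcomes as controls". The test is a paired t-test or Wilcoxon signed-rank test, with multivariable regression for confounders.

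From this design the rationale concludes: "Changes in ARFAs’ outcomes will thereby be attributed to the ACT intervention". The same paragraph grants that the design does not remove the need for randomization. The limitations in the Discussion cover dropout, loss of contact through institutional care and missing data. They do not mention regression to the mean.

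**The concern.** Selection and baseline use the same variable over in effect the same year. A patient's yearly count is a stable level plus a year-specific deviation. Choosing patients because the count is high favours upward deviations, and these are not expected to recur. The next year's mean is therefore lower even without treatment, whenever the year-to-year correlation is below 1. Recruiting the heaviest users first strengthens the effect. Recruiting mainly during hospital visits ties entry to current use as well.

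No untreated series shows how large this fall is. Multivariable adjustment cannot supply it: without an untreated comparison, a regression on the treated patients cannot separate the natural fall from an ACT effect.

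The primary hypothesis is at stake. So is the net cost saving under Secondary outcomes, which is calculated from decreased ED encounters, and with it the policy use that the Discussion foresees.

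**Working it through.** **1. The plan's own figure.** Inputs from Trial flow and sample size: mean 30.15, expected fall 40%, SD 23, power 80%, alpha 0.05 (taken as two-sided).

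- Difference = 0.40 × 30.15 = 12.06 visits.
- n = ((1.960 + 0.842) × 23 / 12.06)² = 28.55, so 29, as stated.
- 29 × 1.15 = 33.4, so 34, as stated. (Dividing by 0.85 gives 34.1, so 35; the difference is immaterial here.)

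The sample size arithmetic is not at fault.

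**2. What the protocol does not give.** It states neither the year-to-year correlation of visits without ACT nor the share of eligible patients recruited. If the SD of 23 is read as the SD of the paired change and 23.47 as the SD in each year, the implied correlation is 1 − 23² / (2 × 23.47²) = 0.52. That reading is an assumption.

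**3. Simple formula.** With a stable pool mean, expected fall = (1 − correlation) × (selected mean − pool mean) / selected mean. Take 30.15 as the mean of an already selected group and assume a correlation of 0.5:

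- pool mean 25: 0.5 × 5.15 / 30.15 = 8.5%
- pool mean 10: 0.5 × 20.15 / 30.15 = 33.4%

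With a correlation of 0.3 and a pool mean of 10: 0.7 × 20.15 / 30.15 = 46.8%.

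**4. Simulation with heaviest users first.** Gamma-Poisson yearly counts, no ACT effect and no trend; at least 5 visits; heaviest users taken until the before-year mean is about 30. The pool mean, gamma shape and year-to-year CV of a patient's rate are assumptions. Chances are for a significant fall in a two-sided 0.05 paired t-test, so the nominal rate in that direction is 2.5%. Ranges span repeated runs.

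| Pool mean, shape, CV | Before mean / SD | After mean | Fall | False benefit, n=34 | False benefit, n=93 |
|---|---|---|---|---|---|
| 8, 0.3, 0.3 | 29.2 / 22.6 | 27.6 | 5.5% | 9–10% | 15–18% |
| 10, 0.5, 0.5 | 30.0 / 22.8 | 26.4 | 12.0% | 18% | 33–36% |
| 5, 0.3, 0.7 | 29.8 / 23.0 | 22.1 | 25.8% | 44–46% | 75–80% |

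The pool changes along with the CV, so this is not a pure CV range. With one pool held fixed, CVs of 0.3 / 0.5 / 0.7 give falls of 7% / 12% / 18% (pool 10, 0.5) or 5% / 10% / 15% (pool 8, 0.3), but the before-year SD then drifts away from 23.

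**5. A second selection model.** Here the mean of 30.15 and SD of 23.47 describe the whole pool. Falls without any ACT effect, by assumed correlation:

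| Selected | 0.3 | 0.5 | 0.7 | 0.9 |
|---|---|---|---|---|
| At least 5 visits only | 3.1% | 2.0% | 1.2% | 0.5% |
| Top 75% of eligible | 14% | 10% | 6% | 2% |
| Top 50% | 25% | 18% | 10% | 4% |
| Top 25% | 37% | 27% | 16% | 5% |

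At a correlation of 0.5 with the top half taken, the chance of a significant fall is 41% at n=29 and 85% at n=93.

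**6. An earlier baseline year.** In the three settings of step 4, the mean for months -24 to -13 is 27.7, 26.5 and 22.0, against after-year means of 27.6, 26.4 and 22.1. The spurious fall disappears, and significant falls return to about 2.5%. This holds because the simulated years are exchangeable around the selection year.

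**The case against.** The before-and-after design is declared openly, and the protocol concedes that it does not replace randomization. The size of the bias rests on assumptions. Step 4 takes users strictly from the top, which leaves out everyone below about 11 to 13 visits and keeps only some 43% to 60% of eligible patients. The protocol admits patients from 5 visits, calls recruitment mainly opportunistic, aims to include everyone in the programme, and gives 30.15 as the mean for ARFAs in general. On that reading the bias may be as small as 0.5% to 3%. This stands, and it is why only a range can be given.

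Three stronger readings are tempting, and the documents support none of them:

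- *A significant reduction is to be expected even if ACT does nothing.* In step 4 this is more likely than not only in the most extreme setting, and there only at n=93.
- *The planned 40% fall would be artefact.* All but the most extreme scenarios stay below 40%.
- *The paired test loses its type I error.* It remains valid for the hypothesis of no change. The fault lies in reading that change as an effect of ACT.

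An earlier baseline year has its own weakness. If use was escalating, months -24 to -13 understate what would have happened without ACT and bias against it, and the longer gap lets in secular trend. It is therefore debatable as the sole primary baseline.

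None of this rescues the attribution sentence. The qualifying year is still the baseline, and no comparison in the protocol absorbs the natural fall.

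**Conclusion.** The point holds on the text. Selection on the before year, priority for the heaviest users and own history as the only control bias the primary comparison, and the cost saving derived from it, in favour of ACT. The direction requires only a year-to-year correlation below 1 and a stable underlying level of use.

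The size is uncertain. It runs from about 0.5% to 3% if nearly all eligible patients are enrolled and average 30 visits, to about 5% to 26% in the matched simulation with the heaviest users first. In the latter case a falsely significant benefit has a chance of about 10% to 45% at n=34 and 15% to 80% at n=93, against a nominal 2.5%. A significant fall therefore cannot be read as an effect of ACT. It does not follow that ACT is ineffective.

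**What to change.** 1. Delete the attribution sentence under Secondary hypotheses. Report the pre-post result as a change, not an effect, and name regression to the mean as a limitation, also for the cost saving.
2. Extract ED counts for months -24 to -13 from the same electronic records. Pre-specify a comparison of the post-intervention year with that non-qualifying year, reported beside the qualifying-year comparison. No causal conclusion should rest on the qualifying year alone. State that the added comparison assumes no secular trend and no escalation in use, and check that the retrospective data consent covers the longer period.
3. Where record access allows, use the staggered start in Table 1. Apply the record-based eligibility criteria at an index date to patients at hospitals not yet started (B before August 2021, C before August 2022, D before August 2023), and estimate a difference-in-differences rate ratio. Note that consent capacity, language and eligibility for ACT services may not be in the records, so the match is partial.

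The cost of items 1 and 2 is one more year of record extraction, possibly a consent check or extension, and some analysis. Item 3 also needs access to records of non-participants, which the retrospective consent described does not evidently cover. Recruitment and treatment are unchanged. The estimated reduction will probably be smaller.

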### Participants

#### Inclusion criteria

Patients at the study site meeting the following criteria are eligible for participation: aged 21 years or older, have recorded a minimum of two alcohol-related and five all-cause visits to an ED in the preceding 12 months, and are fluent in either English or Mandarin. Patients who discontinued ACT but have completed a minimum of three ACT visits are included, considering that significant interventions would have been implemented into their social, drinking, and medical conditions by the third visit.

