#### Trial flow and sample size

A detailed flow diagram is provided (see Fig. 2), demonstrating the progression through the multidisciplinary team-based ACT interventions, occurring parallelly to standard emergency care for ARFAs. The diagram’s numerical annotations are informed by our power analysis during the study design phase. As a real-world implementation study, our recruitment goal encompasses all patients in the ARFA program. According to past data, ARFAs utilize ED services at a mean of 30.15 visits/year, with a standard deviation (SD) of 23.47. With an expected 40% usage decrease, a standard deviation of 23 visits, 80% power, and an alpha of 0.05, we estimate a required sample size of 29 patients. Anticipating a 15% attrition rate, our target recruitment number stands at 34 patients.

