#### The multidisciplinary team-based ACT intervention

Historical patient data are collected from the electronic health record system. We implement a multidisciplinary, team-based ACT intervention, targeting medical, psychiatric/psychological, social and substance (MPSS) domains. The ACT teams follow a predefined schedule, with each engagement spanning approximately 60 min. Interactions include CM and collaboration with a social service agency (SSA). Patients who opt out of the intervention will still be considered in the analysis.

The ACT team will maintain active engagement with ARFAs on a schedule detailed (see S Table 1), with a typical interaction lasting 60 min.

Each visit is not rescheduled in the event of a patient’s absence; instead, the team will re-engage the patient via phone to plan for the succeeding visit as per schedule. Consistent with the core principles of ACT, ARFAs are assertively engaged in the community, receiving intensive, comprehensive, and supportive care with a harm reduction approach. This also incorporates CM and collaboration with a SSA.

A typical ACT visit is as outlined in Fig. 3. “Assertive” in ACT means ACT workers lean forward in terms of patient recruitment and retention. This involves visiting patients in various non-traditional settings including but not limited to hospital admissions, nursing homes and incarceration. If the patient is uncontactable for individual visits, the research worker will go around the vicinity to look for the patient. In the event that a patient falls out with the research worker, an option to switch the research worker is available, as it is a counselling-based intervention.

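### A three-visit attendance condition under the inclusion criteria conflicts with the rules that keep opt-outs in the analysis, and the conditional intention-to-treat analysis does not settle which set is primary

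*Protocol article*

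**What the plan says.** Five places in the protocol article bear on who is analysed.

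- **Inclusion criteria.** After age, prior ED visits and language comes: "Patients who discontinued ACT but have completed a minimum of three ACT visits are included". The reason given is exposure: "considering that significant interventions would have been implemented into their social, drinking, and medical conditions by the third visit".
- **The multidisciplinary team-based ACT intervention.** "Patients who opt out of the intervention will still be considered in the analysis". No minimum number of visits is attached.
- **Screening and recruitment.** "If participants discontinue or deviate from the intervention protocol, we will attempt an exit interview to gather insights and continue collecting relevant outcome data". Again there is no minimum.
- **Trial flow and sample size.** "our recruitment goal encompasses all patients in the ARFA program".
- **Statistical methods.** The first analysis is described as follows: "Using complete set data analysis, cases undergoing ACT will be compared their own historical outcomes as controls". Then: "Should complete set analysis show efficacy, we will proceed to analyze the data using an intention-to-treat analysis".

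The primary outcome, ED visits in the 12 months before and after the intervention, comes mainly from the electronic records of the participating hospitals.

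**The concern.** Inclusion criteria should rest on facts known at enrolment. The number of ACT visits attended is not such a fact. The qualifier on discontinuers has a function only if those with fewer than three visits are treated differently, so it implies that they are left out. Two other sections imply that they stay in.

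At stake is the denominator of the primary result. The study has no concurrent control group; each patient's earlier ED use is the comparator, and the change is to be attributed to ACT. If the analysed patients are those who stayed for three visits, the question moves from what happens to patients who are offered ACT to what happened to those who engaged with it. By the protocol's own reasoning, patients below the cut are the ones who had not yet received enough intervention to count. Leaving them out therefore tends to favour ACT.

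**Working it through.** **1. The rules applied to one patient.** Take a patient who consents, attends one ACT visit and stops.

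| Section | Consequence for this patient |
|---|---|
| Inclusion criteria | Out, by implication (fewer than three visits) |
| ACT intervention | In (opt-outs considered in the analysis) |
| Screening and recruitment | Outcome data still collected |
| Statistical methods, complete set | Unknown; the set is not defined |
| Statistical methods, intention-to-treat | In, unless the three-visit rule is an eligibility criterion; and only if the first analysis shows efficacy |

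No sentence says which rule governs the primary comparison. If the complete set result is not favourable, the text does not commit to an analysis of everyone enrolled.

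**2. The plan's own figures** (Trial flow and sample size). Pre-intervention mean 30.15 visits a year; expected decrease 40%, so 0.40 × 30.15 = 12.06 visits and a post-intervention mean of 18.09. Taking SD 23 as the SD of the paired change, with two-sided alpha 0.05 and 80% power:

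n = (23 × (1.9600 + 0.8416) / 12.06)² = 28.55, rounded up to 29.

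This reproduces the stated 29. The target of 34 follows from 29 × 1.15 = 33.35. Dividing instead, 29 / 0.85 = 34.1, gives 35. The sample size is not in dispute here.

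**3. Effect of dropping early leavers.** Let f be the share of enrolled patients who leave before visit 3, R_ret the reduction in those retained, and R_early the reduction in early leavers. With the same pre-intervention mean in both groups (an assumption):

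R_all = (1 − f) × R_ret + f × R_early.

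If R_early = 0, then R_ret / R_all = 1/(1 − f). The article gives no value for f or R_early, so both are assumed below. R_ret is set at the planned 40%.

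| f | Early leavers' ED use | All-enrolled post mean | R_all | R_ret / R_all |
|---|---|---|---|---|
| 10% | unchanged (30.15) | 0.9 × 18.09 + 0.1 × 30.15 = 19.30 | 36% | 1.11 |
| 20% | unchanged (30.15) | 0.8 × 18.09 + 0.2 × 30.15 = 20.50 | 32% | 1.25 |
| 40% | unchanged (30.15) | 0.6 × 18.09 + 0.4 × 30.15 = 22.91 | 24% | 1.67 |
| 20% | up 20% (36.18) | 0.8 × 18.09 + 0.2 × 36.18 = 21.71 | 28% | 1.43 |
| 20% | down 20% (24.12) | 0.8 × 18.09 + 0.2 × 24.12 = 19.30 | 36% | 1.11 |
| 20% | down 40% (18.09) | 18.09 | 40% | 1.00 |

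If early leavers fell by more than 40%, the sign would reverse and the three-visit set would understate the effect.

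**4. No average change overall.** With R_all = 0 and early leavers up 20%, the retained set would show a spurious reduction of 0.20 × f/(1 − f): 2.2% at f = 10% and 8.6% at f = 30%.

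**The case against.** The best defence is that the article names two analyses. On that reading the three-visit sentence defines who counts as treated in the complete set, and the promise about opt-outs is kept by the intention-to-treat analysis. The exposure rationale fits an analysis-set definition better than an eligibility rule. Exclusion criteria does not list fewer than three visits, and outcome collection continues for everyone. This is a fair reading, but the article never links the three-visit rule to the complete set, and the intention-to-treat analysis is conditional on a favourable first result. The defence explains what may have been meant; it does not remove the conflict.

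Three stronger inferences are tempting, and the text does not support them.

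- **That early failures are certainly removed.** Exclusion of patients with 0 to 2 visits is implied by the qualifier and stated nowhere.
- **That the rule removes the known defaulters.** Background says "ARFAs frequently default, particularly within the initial three months", but that concerns recommended addiction treatment in general, not ACT, and three months is not three visits. The protocol has 17 visits and the schedule is in a supplement not shown here, so visit 3 may come well before three months.
- **That the effect is certainly inflated.** Patients are chosen for high prior use, with the most frequent users given priority, so regression to the mean could lower early leavers' counts too. Discussion also notes that institutionalisation through ACT may cause loss of contact, and such patients might have fewer ED visits.

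Nor does the rule undermine the 15% attrition allowance in any important way. That figure only moves 29 to 34, while Table 1 allows up to 340 patients (136 + 102 + 68 + 34) and 93 had been recruited by March 2023.

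**Conclusion.** The concern holds as an unresolved contradiction about the primary analysis set. A condition known only after enrolment stands among the inclusion criteria, conflicts with two other sections, and is not reconciled by Statistical methods. Followed as written, it selects the before-after set on adherence.

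Overstatement of the reduction is the likely direction, not a certain one. Its size is 1/(1 − f) if early leavers do not change: 40% reported against 36% at f = 10%, or 32% at f = 20%. These figures rest on assumed values of f, on equal pre-intervention means in the two groups, and on no change in early leavers; the difference shrinks to nothing as their improvement approaches that of retained patients. The article does expect a high dropout rate, so f may not be negligible, but it cannot be estimated from the article.

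**What to change.** - Remove the three-visit sentence from Inclusion criteria, so that eligibility rests on facts known at enrolment.
- Define the primary analysis set as all consented patients from enrolment, with ED visits taken from the electronic records whatever their ACT attendance. This agrees with the sections on opt-outs and on continued outcome collection.
- Run that analysis unconditionally, and delete the clause that makes intention-to-treat depend on the complete set result.
- Define the complete set, or replace it with a labelled supplementary set of patients with at least three ACT visits. Report how many patients it excludes.

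The cost is a change of wording. No new data source is needed for the primary outcome, because ED visits do not depend on attendance at ACT visits. The downside is a probably less favourable point estimate and some loss of power: if early leavers do not change, the required n becomes 28.55/(1 − f)², which is 36 at f = 10% and 45 at f = 20%. The 93 patients already recruited exceed both, before any loss of outcome data.
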